# Study protocol: implementation of a computer-assisted intervention for autism in schools: a hybrid type II cluster randomized effectiveness-implementation trial

**DOI:** 10.1186/s13012-016-0513-4

**Published:** 2016-11-25

**Keywords:** Effectiveness-implementation trial, Exnovation, De-implementation, Computer-assisted intervention

## Abstract

**Background:**

The number of children diagnosed with autism has rapidly outpaced the capacities of many public school systems to serve them, especially under-resourced, urban school districts. The intensive nature of evidence-based autism interventions, which rely heavily on one-to-one delivery, has caused schools to turn to computer-assisted interventions (CAI). There is little evidence regarding the feasibility, effectiveness, and implementation of CAI in public schools. While CAI has the potential to increase instructional time for students with autism, it may also result in unintended consequences such as reduction in the amount of interpersonal (as opposed to computerized) instruction students receive. The purpose of this study is to test the effectiveness of one such CAI—TeachTown—its implementation, and its effects on teachers’ use of other evidence-based practices.

**Methods:**

This study protocol describes a type II hybrid cluster randomized effectiveness-implementation trial. We will train and coach 70 teachers in autism support classrooms in one large school district in the use of evidence-based practices for students with autism. Half of the teachers then will be randomly selected to receive training and access to TeachTown: Basics, a CAI for students with autism, for the students in their classrooms. The study examines: (1) the effectiveness of TeachTown for students with autism; (2) the extent to which teachers implement TeachTown the way it was designed (i.e., fidelity); and (3) whether its uptake increases or reduces the use of other evidence-based practices.

**Discussion:**

This study will examine the implementation of new technology for children with ASD in public schools and will be the first to measure the effectiveness of CAI. As importantly, the study will investigate whether adding a new technology on top of existing practices increases or decreases their use. This study presents a unique method to studying both the implementation and exnovation of evidence-based practices for children with autism in school settings.

**Trial registration:**

NCT02695693. Retrospectively registered on July 8, 2016.

## Background

Autism spectrum disorder (ASD) is characterized by impairments in socialization and communication and is accompanied by highly restricted interests and repetitive behaviors [1]. The number of children with autism in special education has increased an average of 17% a year for the past 15 years [2]. This increase places a significant financial burden on schools. Evidence-based autism interventions are expensive, requiring skilled interventionists working with children individually or in small groups for up to 25 h per week [3]. The average annual expenditure per pupil with autism is three times that of children in general education and twice that of other children in special education [5]. While there is little description of services associated with this elevated expenditure [4, 6–9], it is likely that much of the increase comes from the use of these intensive interventions [10].

In recent years, computer-assisted interventions (CAI) have gained popularity as a method for educating children with ASD [11]. Many CAI have integrated evidence-based instructional strategies for children with ASD [7, 12–17]. CAI is appealing to under-resourced schools because of the potential to provide cost-effective individualized instruction while freeing up teachers to provide concurrent group instruction.

Most studies of CAI are descriptive and exploratory, and employ small samples with single-subject research designs [16, 18]. Preliminary findings indicate promising results for academic, social, and language outcomes, with anecdotal improvements in behavior and compliance during instructional time [19–21]. Overall, however, the use of CAI for students with ASD has outpaced the evidence for its efficacy [12]. A notable exception is TeachTown: Basics, a CAI that includes computerized lessons combined with teacher-delivered interpersonal instructional activities. In a randomized trial, students who received instruction using TeachTown improved more on language and cognitive outcomes than students in a control group after 3 months of intervention [22]. The study sample was small, however, and the study was conducted in only a few classrooms.

New technologies like TeachTown could have unintended consequences or be implemented in unexpected ways. For example, teachers may choose to implement some components of TeachTown and not others. They also may perceive that TeachTown can substitute for existing practices and change other instructional approaches as a result. Understanding the factors that affect the implementation of CAI and how the implementation of CAI affects teachers’ use of other evidence-based practices is critical for evaluating their effectiveness, feasibility, and sustainability in under-resourced public schools.

The purpose of this hybrid effectiveness-implementation [23] study is to (1) assess the effectiveness of the TeachTown program in improving the outcomes of youth with ASD using a randomized trial in an urban public school district, (2) understand how teachers implement this new technology within their classrooms and the factors that affect implementation, and (3) evaluate how existing evidence-based practices (EBP) change when a new technology is introduced.

We hypothesize that TeachTown will be associated with improvements in children’s cognitive ability and academic skills. Our hypotheses about factors affecting TeachTown implementation, and what will happen to existing practices when TeachTown is introduced, are driven by a conceptual model that combines well-established theories of behavior with organizational variables. Williams and Glisson propose a similar model that integrates organizational context and behavioral intention [24], which we have expanded by adding the determinants of intention: attitudes, norms, and self-efficacy (Fig. 1).

**Fig. 1 Fig1:**
[figure not shown]
Conceptual model

At the core of our model is the theory of planned behavior, which posits that individuals’ intention to perform a certain behavior is the most proximal determinant of that behavior, when individuals have the ability to act on their intentions. The determinants of intention are attitudes (e.g., whether one “likes” or “dislikes” using a given EBP), norms (e.g., whether one perceives that using a given EBP is viewed as appropriate by others), and self-efficacy (e.g., whether one believes that one has the necessary skills to perform the EBP). This model is commonly used to predict health behaviors and is gaining currency as a tool for understanding mental health clinicians’ adoption of evidence-based practices [25], as well as teachers’ behavior, including use of educational technology [26] and different curricular and teaching approaches [27–31].

This model motivates two sets of hypotheses. First, we hypothesize that a strong organizational context, defined as climate for innovation implementation [32] will positively influence the determinants of intention and result in greater use of TeachTown, as will the presence of greater IT support (pathway A). Second, we hypothesize that schools’ organizational context and IT support will moderate the association between intentions and behavior, such that, among teachers with strong intentions to use TeachTown, better support will result in greater use (pathway B).

For the past 8 years, our team has provided extensive training and coaching to autism support teachers in the use of several EBPs for children with ASD. The second set of hypotheses relate to teachers’ use of the EBPs in which we have trained them (aim 3). For this aim, we conceptualize TeachTown as a new technology that affects the organizational context and teacher behavior. TeachTown may influence teachers’ attitudes, norms, and self-efficacy about the use of existing EBP (pathway A) and moderate the association between their intentions to use these practices and their behavior (pathway B). Specifically, we hypothesize that introducing TeachTown will negatively affect teachers’ attitudes, norms, and perceptions about using existing EBP, and that teachers will “exnovate” existing practices when they adopt TeachTown. Exnovation refers to the “process whereby an organization decides to divest itself of an innovation that it had previously adopted.” [33–35] Introducing a new technology may result in one of three exnovation outcomes: full exnovation (the new technology completely replaces the previous one so that there is no trace of the previous practice), partial exnovation (the new technology replaces parts or components of the previous practice), or no exnovation (the new technology does not replace the previous practice). We hypothesize that the introduction of TeachTown will result in partial exnovation of EBPs. Teachers may reduce their use of EBP because they think that TeachTown is a reasonable (and easier) substitute for practices like one-to-one instruction or data collection. Our second competing hypothesis is that introducing TeachTown changes the organizational context by giving teachers a tool to provide unsupervised instruction to some students, which would increase the time the teacher has to work with other students. In this case, we would expect use of EBP to increase in classrooms with TeachTown.

TeachTown may be a feasible intervention that improves outcomes for children with ASD in public schools that is well suited for under-resourced settings. On the other hand, there may be negative consequences of implementing CAI, such as reduced use of existing EBPs, which should be weighed against potential benefit. The proposed study offers a novel opportunity to test the effectiveness and implementation of a promising CAI and concurrently increase our understanding of what happens to existing practices when new ones are introduced. Accordingly, we rely on a hybrid effectiveness-implementation design [36], in which the primary outcome is effectiveness, but where we also examine the association of organizational and teacher characteristics with TeachTown and EBP implementation.

## Methods

### Setting

The study will occur in the School District of Philadelphia, the eighth largest school district in the country. The majority of students served by the school district are ethnic minorities (69%); 75% live below the poverty line. The district has attempted to improve access to evidence-based interventions for students with ASD by supporting the implementation of a comprehensive treatment package (Strategies for Teaching based on Autism Research: STAR), consisting of a set of evidence-based practices for the treatment of ASD, in autism support classrooms. As part of the current study, we will provide consultation and training to teachers in the use of the EBP in which we have provided training for the past 8 years. Our coaches provide didactic training in a group setting, as well as in vivo coaching in each classroom regarding the use of the EBPs.

### Participants

#### Teachers

Teachers in the School District of Philadelphia’s K-2 autism support classrooms (*n* = 83) will be recruited. Teachers will participate in TeachTown training as part of their professional development but will not be required to participate in this study. We anticipate recruiting 80% of teachers (69 classrooms). Teachers will be randomly assigned to one of two conditions during year 1 of the study: TeachTown and waitlist. Teachers in the waitlist condition will receive training and support in the use of TeachTown in year 2 of the study.

#### Children and their families

By district regulation, children in K-2 autism support classrooms will be between the ages of 5 and 8. The recruitment goal for the study is 4–5 students in each of the 69 classrooms (which usually have 8 students), for a total of 276 participants. Inclusion criteria are that children have an educational classification of autism and be enrolled at least half time in a K-2 autism support classroom. The one exclusion criterion is if the primary caregiver does not speak English or Spanish, which would exclude <1% of eligible participants.

### Overview of intervention

TeachTown: Basics is a CAI that includes off-computer interpersonal activities, automatic data collection and reporting, and a note system for communication with the child’s team. The curriculum is designed for children developmentally aged 2–7 years, which describes the vast majority of our potential sample.

#### *Computer-assisted instruction*

The computer lessons incorporate the principles of ABA, using a discrete trial format [37], in which the student is provided with a specific instruction, and selects the correct response. Correct responses are immediately reinforced using animated reward games, verbal praise, and graphics. The lessons use specific prompting procedures, such as fading and highlighting the correct answers, to promote success. The curriculum progresses through five levels, and students’ progress at their own pace. The curriculum content addresses six domains: (1) adaptive skills, (2) cognitive skills, (3) language arts, (4) language development, (5) mathematics, and (6) social emotional skills. Progress monitoring is part of the program. Students complete pre-tests and must demonstrate mastery before progressing to the next lesson. Teachers are asked to have the child spend 20 min per day on the software either with the teacher, an aide, or independently.

#### *Off-line activities: interpersonal lessons*

Teachers provide interpersonal lessons via direct instruction. These lessons focus on the same areas targeted in the CAI activities; however, the lessons are designed to promote expressive language and interaction skills. Lesson plans and cues for instructional delivery are included with the program.

### Teacher training in TeachTown

Consistent with best practices [38–40], teachers in the intervention group (and the control group in year 2) will receive 2 days of didactic training at the start of the school year, with experiential components, webinars throughout the school year, and monthly consultation. Training and monthly consultation in TeachTown will be provided by the program developers.

#### Aim 1: effectiveness: How does TeachTown affect student outcomes?

We will examine to what extent TeachTown is associated with student gains in cognitive ability, language skills, school readiness, and social skills. We hypothesize that use of TeachTown will be associated with improved student outcomes in these domains.

### Measures

Our primary outcome of interest, in keeping with recent randomized trials of autism interventions, is cognitive gain. Other selected measures are tied to the domains in which TeachTown purports to affect change (see Table 1).

**Table 1 Tab1:** List of measures, respondents, and time points for data collection

Measure	Respondent	Time point
Aim 1: Effectiveness		
Differential Ability Scales, 2nd Edition (DAS-II)	Direct observation of student functioning completed by graduate student or clinician	Beginning and end of year 1
Bracken Basic Concept Scales, 3rd Edition	Direct observation of student functioning completed by graduate student or clinician	Beginning and end of year 1
Autism Diagnostic Observation Schedule—2nd edition (ADOS-2)	Direct observation of student functioning completed by graduate student or clinician	Throughout year 1
Adaptive Behavior Assessment System, 2nd Edition (ABAS-II)	Teacher rating form of child functioning	Beginning and end of year 1
Pervasive Developmental Disorder Behavior Inventory (PDD-BI)	Teacher rating form of child functioning	Beginning and end of year 1
Social Communication Questionnaire (SCQ)	Parent rating form of child functioning	Beginning of year 1
Family Demographic Questionnaire	Parent	Beginning of year 1
Teacher Demographic Questionnaire	Teacher	Beginning of year 1
Aim 2: Implementation		
TeachTown penetration	Computer software logs	Monthly
TeachTown fidelity	Direct observation of teacher behavior conducted by TeachTown staff	Monthly
Intentions and attitudes scale	Teacher rating scale	Mid-year years 1 and 2
Aim 3: Exnovation		
Existing EBP fidelity	Direct observation of teacher behavior conducted by trained research assistants	Monthly

*Cognitive ability* will be assessed using the Differential Ability Scales, 2nd Edition (DAS-II) [41]. The DAS-II assesses cognitive abilities that are important to learning and may be administered to children ages 2 years 6 months through 17 years 11 months across a broad range of developmental levels. A member of the assessment team will administer the DAS-II to students in the study at the beginning and end of the academic year in year 1.

*Adaptive skills* will be measured using the Adaptive Behavior Assessment System, 2nd Edition (ABAS-II) [42]. The ABAS-II uses a behavior-rating format to assess adaptive behavior and related skills for individuals, birth through 89 years of age. Teachers will complete the ABAS-II at the beginning and end of the academic year in year 1.

*School readiness skills*, including *language arts*, *language development*, and *mathematics*, will be measured using the Bracken Basic Concept Scale—3rd Edition [43]. This scale assesses knowledge of concepts associated with pre-academic skills, such as colors, letters, numbers/counting, sizes, comparisons, and social concepts like social relationships and emotions [44–46]. A member of the assessment team will administer the Bracken at the beginning and end of the school year in year 1.

*Social skills and pragmatic language* will be measured using the Pervasive Developmental Disorder Behavior Inventory (PDD-BI) [47]. The PDD-BI is a rating scale that assesses problem behaviors, social skills, language skills, and learning or memory skills in children who have been diagnosed with autism. It can be used with children between the ages of 1.6 and 12.5 years. The teacher report version of the PDD-BI will be administered by a member of the assessment team at the beginning and end of the academic year in year 1.

#### *Autism classification*

All children in the study will have an educational classification of ASD provided by a school psychologist as part of their educational evaluation. Autism diagnoses will be confirmed in our sample using the Social Communication Questionnaire (SCQ) [48], a parent-report measure that examines the presence of autism spectrum disorder (ASD) symptoms in children, and the Autism Diagnostic Observation Schedule—2nd edition (ADOS-2), administered to 20% of the sample.

#### *Demographic survey*

A parent or guardian will complete a form that includes demographics, family composition, education, and financial resources using the relevant US Census Survey questions.

### Data collection

#### *Direct observation measures*

Members of the assessment team will visit each school at baseline and the end of the academic year to administer the DAS-II and Bracken. The team will meet weekly to maintain 90% reliability on these measures.

#### *Parent report measures*

Parents will complete the demographic survey and SCQ at baseline. Parents will be requested to mail in the form, with follow-up phone calls to increase the response rate. They will receive $50 for completing the forms.

#### *Teacher report measures*

Classroom teachers will complete the ABAS and the PDD-BI for each student enrolled in the study at the beginning of the year and again at the end of the academic year in year 1. Teachers will receive $20 per child for each wave of data collection.

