### Data analyses

Analysis will be based on randomization of classrooms to TeachTown (*n* = 35) or control (*n* = 34). Outcomes will be analyzed at the student level across time. Outcome differences will be estimated with longitudinal nested linear models with random effects for classroom and student [49–51]. All outcome measures are continuous variables.

We also will examine several potential moderators of TeachTown impact, including: (1) symptoms at baseline (measured by the PDDBI); (2) cognitive functioning at baseline (measured by the DAS); (3) penetration (whether the consented student received TeachTown instruction based on the electronic logs); (4) fidelity of program implementation (direct observation of generalization lessons, described in aim 2); (5) use of the EBPs described in Aims 3; and (6) family characteristics, including family composition and parent education and income. Potential moderators will be included in the model as main effects and as interaction terms with time and treatment group factors in the model. The three-way interaction between time, treatment group, and the moderator will be used to assess the presence and magnitude of the moderating effect. Because both TeachTown and EBP fidelity may vary over the course of the year for each student, we will use growth mixture models to categorize fidelity trajectories at the student level.

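### The adaptive (ABAS-II) and social (PDD-BI) outcomes of Aim 1 are rated only by unmasked classroom teachers, so an arm difference on them cannot on its own show effectiveness

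*Protocol article*

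**What the plan says.** Aim 1 of the protocol article sets out to examine "student gains in cognitive ability, language skills, school readiness, and social skills". Table 1 places the DAS-II, Bracken, ABAS-II and PDD-BI together under its effectiveness heading, and lists the last two as teacher rating forms.

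- **Adaptive skills** (Measures): "Teachers will complete the ABAS-II at the beginning and end of the academic year in year 1".
- **Social skills and pragmatic language** (Measures): the instrument is the PDD-BI, and "The teacher report version of the PDD-BI will be administered by a member of the assessment team", in both waves.
- **Who fills in the forms** (under Teacher report measures in Data collection): "Classroom teachers will complete the ABAS and the PDD-BI for each student enrolled in the study at the beginning of the year", with a second wave at year end.
- **Primary outcome** (Measures): cognitive gain on the DAS-II, tested directly: "A member of the assessment team will administer the DAS-II to students in the study". The Bracken is also given directly.
- **Raters' position** (Participants; Overview of intervention; Teacher training in TeachTown): teachers are randomized to TeachTown or waitlist. TeachTown-arm teachers get "2 days of didactic training at the start of the school year" from the developers, with monthly consultation, and give the off-computer lessons themselves. Waitlist teachers are trained in year 2.
- **Moderator** (Data analyses): one of several is "symptoms at baseline (measured by the PDDBI").

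**The concern.** Each form has one kind of rater, and that rater cannot be masked. In one arm the rater has been trained by the program's developers, is coached by them all year and has put effort into delivering the program. In the other arm the rater has not. If that makes TeachTown teachers score their pupils more favorably at year end, the analysis will show a gain even where the children have not changed differently.

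At stake is the social and adaptive part of the Aim 1 conclusion. Social skills are named in the aim itself; adaptive skills enter through the measures text and Table 1. Nothing in the article limits what a positive teacher-rated result may be taken to show.

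**Working it through.** **1. Is there any other measure of these two domains?** Adaptive skills: ABAS-II only. Social skills and pragmatic language: PDD-BI only. The Bracken includes social concepts, but it tests what a child knows, not how the child behaves. The parent-completed SCQ is collected at baseline only, to confirm diagnosis. So no independent rating can check either outcome.

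**2. What does the model estimate?** For a teacher-rated score, the expected arm contrast is

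true effect + (mean rating bias in TeachTown − mean rating bias in waitlist).

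Arm and rater type coincide in year 1, so classroom and student random effects cannot separate the two terms.

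**3. The plan's own precision.** Inputs (Statistical power for quantitative analyses): 80% power at d = 0.43, 4 students per classroom, ICC 0.2, one covariate with R² = 0.15, two-sided 0.05, 70 classrooms. Data analyses gives 35 + 34 = 69 classrooms.

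Without the covariate, SE = √{[0.2 + 0.8/4]/(0.25 × 70)} = 0.1512, and power at 0.43 is 80.1%. With the covariate it is 83% to 86%, depending on the level at which it acts. The stated 80% is thus matched only without the covariate and is somewhat conservative. The point here does not depend on this.

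**4. Illustration of the consequence.** The documents give no size for rating bias, so b is assumed. It is the net bias, in SD, left in the treatment contrast when the true effect is zero.

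- *(A) Back-calculated from the stated power:* SE = 0.43/(1.960 + 0.842) = 0.1535. P(significant) = 1 − Φ(1.960 − b/SE) + Φ(−1.960 − b/SE). For b = 0.2: b/SE = 1.303, giving 0.256.
- *(B, C) From the cluster variance:* 69 classrooms, covariate at both levels, noncentral t with 66 df. SE = √{0.85 × [ICC + (1 − ICC)/4]/(0.25 × 69)}, which is 0.1404 at ICC 0.2 (B) and 0.1646 at ICC 0.4 (C). The ICC of 0.4 is also an assumption: one teacher scoring all enrolled children in a class could raise clustering.

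| Assumed net bias b | A | B: ICC 0.2 | C: ICC 0.4 |
|---|---|---|---|
| 0 | 5% | 5% | 5% |
| 0.1 SD | 10% | 11% | 9% |
| 0.2 SD | 26% | 29% | 22% |
| 0.3 SD | 50% | 56% | 44% |

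**5. Does a shifted baseline PDD-BI spoil the moderator test?** Let G be arm, T time and M the true baseline score, and let the recorded score be M + cG, with c a constant shift in the TeachTown arm. Because G is 0/1, T·G·(M + cG) = T·G·M + c·T·G. The extra piece is absorbed by the T·G term, and the shifts in the lower-order terms are absorbed likewise. The three-way coefficient, which the plan uses to judge moderation, is unchanged. Distortion would need rating error that varies with the child's severity or response.

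**The case against.** **The article already has a hierarchy.** Cognitive gain on a direct test is named as primary and the rest are other selected measures. That stands, and it limits the point to the secondary teacher-rated outcomes. It does not remove it, because Table 1 and Aim 1 still count those outcomes as effectiveness without qualification.

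**The raters are not all trained deliverers.** True: about half are waitlist teachers, untrained in TeachTown during year 1. This contrast is what makes the bias differential.

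**The illustration is only that.** Every bias size is assumed. If baseline ratings were inflated too, part of the bias would cancel in the gain. Both remarks are fair, so the table shows sensitivity, not an estimate.

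**A reader might infer that the primary outcome is biased**, since "The teacher report version of the PDD-BI will be administered by a member of the assessment team" and the same team tests the DAS-II. The documents do not support this. They refer each time to one member of the team without saying it is the same person. They say nothing on masking, which the full protocol may cover. Handing over a form is compatible with the teacher filling it in, and the team visits the schools anyway.

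**A reader might also infer that baseline ratings are contaminated and the symptom moderator biased.** Training and baseline rating fall in the same start-of-year window, but their order is not given. A constant arm-wide shift would leave the moderator coefficient unchanged.

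**Conclusion.** The point holds for the ABAS-II and PDD-BI as Aim 1 outcomes. Each has a single unmasked rater whose stake differs by arm, and no analysis of the planned data can tell expectation from child change. Its size cannot be fixed from the documents. At assumed net biases of 0.1, 0.2 and 0.3 SD, the false-positive rate would be about 10%, 26% and 50% using the precision implied by the stated power, and about 9%, 22% and 44% at an assumed ICC of 0.4. The direction is stable across these assumptions, and the exact percentages should not be relied on.

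The point does not extend to the DAS-II, the Bracken or the symptom moderator. Bias in these is neither stated nor shown, and the primary conclusion is not put in doubt.

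**What to change.** 1. In Aim 1 and its Measures section, state that the effectiveness conclusion rests on the DAS-II and Bracken. Designate the ABAS-II and PDD-BI as unmasked, teacher-rated supportive outcomes that cannot alone support a claim on social or adaptive skills. Cost: wording, and a narrower claim in those two domains.
2. As a precaution, reconcile the Measures text on who administers the PDD-BI with Teacher report measures. Let teachers complete it themselves, and have the research assistants who already observe classrooms handle the forms, rather than the DAS-II and Bracken testers. Cost: reallocation of a small task among existing staff.
3. Where scheduling allows, take the baseline teacher ratings before TeachTown training. Where it does not, do not describe them as pre-intervention scores. Cost: some scheduling at the start of the year. Insisting on this order everywhere could delay training and shorten year-1 exposure, so it should stay conditional.
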